## *IV.B. Intervention and routine activities*

To prepare the implementation of interventions, a workshop with the health area responsables for vector control and a workshop with formal and informal community leaders will be held to discuss the detailed implementation planning, as also a meeting with the population of every health area involved to inform them about the trial and answer questions concerning tools and its implementation.

Insecticide treated Curtains (ITC):

The insecticide-treated curtains (ITC) to be used are made from long-lasting, insecticide treated (pyrethroid deltamethrin is applied during manufacture) polyester netting that requires no re-impregnation (PermaNet®; Vestergaard-Frandsen company). PermaNet materials are special UV protected and retain their insecticidal properties and efficacy for about 2 years (information from producer). The material has been approved by WHOPES for use as bednets. ITC will be distributed in each house to be placed in door-openings inside the house or on the closet or on the wall where no or minimal sunshine will touch the material - if a curtain is already hanging, the project-curtain can be attached to it. Per house a maximum of 3 curtains will be distributed, except for schools, working areas and public spaces where more curtains can be distributed.

All curtains will be white patterned netting and have a 1.1m width*2.9m height size (people can adapt them according their needs).

Before distribution the consent of the users will be procured in a community meeting and a written informed consent-form will be obtained (annex 1).

The curtains will be distributed with an accompanying promotion campaign: a Frequently Asked Questions document (FAQ) is already elaborated (annex 2). It will be given to all included households in the ITC arm and will be discussed during distribution on individual basis.

The curtains will be distributed to the houses, but also public places, as working areas, schools, cultural centra will be included as far as possible.

A replacement of curtains will be foreseen for the curtains becoming damaged during use. If new persons are coming to live in the house-blocks during the study, they will be approached to be included in the study.

The procedure of distribution is detailed in annex 3.

Peri-focal insecticide spraying (PFS)

K-Othrine 25 WG, supplied by Bayer Environmental Sciences co. (25% deltamethrin formulation) will be sprayed every 4 months (3 times/year). It is a granular formulation that need to be solved into water (20 gram in 8 Liter of water, sufficient to treat 200 m² and attaining 25 mg a.i./m²). It has a long lasting residual activity. Where deposits remain undisturbed, residual activity depends upon the nature of the surface (Rojas de Arias et al. 2004;Rozilawati et al. 2005). Sustained residual activity beyond 12 weeks post-application is observed on non-porous surfaces. Deltamethrin is photostable and the particulate suspension enhances availability to insects.

The insecticide will be sprayed on the outside of the ground-level water tanks and the walls behind them; and on the adult *Aedes* resting sites (for example under beds, in and under closets) in the intradomestic area.

Teams of health workers of the routine *Aedes* control programme will be trained to realize this activity and standard operating procedures are designed. A short movie has been made to show the correct application of insecticide to all implementers. Control visits by supervisors will be done on a regular basis during application to assure quality of action.

The PFS will be done in the houses, but also public places, as working areas, schools, cultural centra will be included as far as possible.

Before distribution the consent of the users will be procured in a community meeting and a written informed consent will be obtained on the moment of spraying. Information on the product and its possible side effects will be provided to the communities in the preparative community meetings and to each household before spraying starts.

The procedure of implementation is detailed in annex 4.

The set-up of the ITC and PFS interventions will be done by a local research group and by the routine vector control programme. The former will be responsible for its implementation, coordination with the local health authorities, documentation of process and organization of training sessions according to the needs of the actors involved.

Routine *Aedes* Control activities

In all arms, the routine control activities will be continued. In the control-arm, this will be the only strategy. The standard control activities are carried out by the programme’s vector control workers: entomological surveillance and source reduction through periodic inspection of houses, larviciding (with temephos) of water-holding containers, selective adulticiding (cipermethrine and clorpiriphus-fogging) when *Aedes aegypti* foci are detected, providing health education, promotion of community based environmental management and enforcing mosquito control legislation through the use of fines.

## *IV. C. Data collection and analysis*

Effect measures:

Primary outcomes:

Effectiveness: Breteau Index, House index, Pupae per person index, (adult mosquito infestation)

confirmed Dengue cases (if any). Comparison of infestation at each time point between the intervention arms, taking into account the pre-intervention infestation levels and the cluster design. Generalized linear random effect regression models with a negative binomial link function will be used.

Secondary output:

Uptake and use of ITC

Acceptance of PFS and ITC (and identification of underlying lay dimensions of acceptability)

Change in intra-and extradomiciliary risks for Aedes infestation

Cost- effectiveness of ITC and of PFS

Residual insecticidal activity of deltamethrin applied in ITC and in PFS

Data collection:

1. Baseline study (in both intervention and control arms) :
   1. Entomological survey:

Existing of larval and pupal surveys; the larval surveys will be conducted as in the routine system (exhaustive inspection of all houses and potential water holding containers on the presence of immature stages of Aedes). The traditional Stegomyia indices will be calculated: the House Index (HI) and Breteau index (BI). Collection of adult mosquitoes: during routine surveys, the vector control teams are also inspecting houses in the search of adult mosquitoes.

The pupal surveys will consist of direct inspection of potential water-holding containers inside and around the houses following the recommendations of Focks (Focks 2004). This will be done by a special team in 20% of the house-blocks (randomly chosen: 23 houseblocks/arm). All containers where immature stages of Aedes are detected will be emptied and the absolute number of pupae will be counted. For elevated water tanks a sweeping method will be used to collect the majority of the pupae. The total number of positive containers for Ae. aegypti pupae and their relative contribution to total pupal production will be recorded and computed. The number of persons per house will be also enquired (during the distribution of tools) for the construction of Pupal Index per inhabitant (PPI) at the cluster level.

- 1. Evaluation of main intra and extra domiciliary risks at household and environmental risks at community level in each houseblock included in the study: data collected by the routine vector control programme teams through observation, guided by an observation guide (Annex 5).
  2. Evaluation of resistance of the local Aedes strains to the four groups of adulticides commonly used for mosquito control (report, including methodology, in annex 6).

1. Follow-up surveys:
   1. Entomology (in both intervention and control areas):

The same measurements as in the baseline entomological study will be done once intervention started (House Index (HI), Breteau index (BI), Pupal Index per inhabitant (PPI)). The frequency of the larval surveys (including the collection of adult mosquitoes) will be according the cycles taking place by the routine control programme, with at least one survey per month. The pupal surveys will take place twice a year during the peak periods of infestation (end of April and end of September).

- 1. Surveillance of Dengue cases (confirmed) and epidemiology of clinical Dengue cases if an epidemic occurs in the period of study (in both intervention and control areas)
  2. Observation of main intra and extra domiciliary risks at household and environmental risks at community level (data collection as explained above; frequency once/year) – (Annex 5) (in both intervention and control areas)
  3. Uptake and use of curtain (in ITC intervention area)

Uptake and continued use will be evaluated every 4 months over a period of 2 years. The teams will use an observation guide during the household visits (Observation guide: annex 7).

- 1. Registration of executed vector control activities: besides information available in reports of the *Aedes* control programme, information will be obtained from community perspective (Questionnaire: annex 8) (in both intervention and control areas)

Every 4 months, one in 30 households will be questioned concerning the vector control activities (by community or by routine vector control programme) that were realized in the previous period.

- 1. Evaluation of acceptance, use and satisfaction of specific control measure (in intervention areas):
     1. ITC: through household surveys, 4 , 12, 24 months after distribution (in a sample of 400 houses, systematic random sampling – able to detect a 50% acceptance with 5% precision) (data collection form: annex 9)
     2. PFS: through household surveys, 4 , 12, 24 months after distribution (in a sample of 400 houses, systematic random sampling – able to detect a 50% acceptance with 5% precision) (data collection form: annex 10)
  2. Residual activity/bio-availability testing (in intervention areas):
     1. ITC (monitoring insecticide content of PermaNet curtains over time): These bioassays will be done using two methods of exposure: cone method and tube method. In both, the same procedure will be followed: 10 cones/tubes per curtain, 5 female *Aedes* mosquitoes per cone/tube, 3-5 days old, non-blood fed, exposure of 3 minutes, evaluation of knock down after 3’ and 1 hr and mortality after 24 hr. This will be done at 4 time moments (or shorter if decline of residual effect): on a sample of 2 curtains before distribution (non-used ITC to evaluate batch quality), on a sub-sample of 10 curtains, after 6, 12, 18 and 24 months of use. In the 6 month assay, ITC will be collected in 10 houses of vector control workers (where washing procedures and washing frequency and other characteristics of use will be recorded in a prospective way). In the surveys of 12 and 24 months, a random sampling will be done. Additionally a subsample of the curtains (one ITC which gives mortality below 80%, one with mortality between 80-95% and one with mortality > 95%) will be evaluated through HPLC to define the residual deltamethrin concentration (Laboratorio de registro de plaguicidas en Cuba, a certified center in Havana).
     2. PFS:
        - Bio-assays (cone method, with 15 female *Aedes* mosquitoes/cone; 3-5 days old, non-blood fed, exposure of 1 hour – transference to clean cups, observation of knock down/mortality after 1 hour and after 24 hours)
        - Selection of houses: 4 houses (one per health district) with previous indication of surfaces to be tested; and 4 houses (randomly chosen, one per district) with no previous indication of surfaces to be tested
        - Test of : 2 cones on metal surface; 2 cones on wooden surface, 2 cones on cement surface and 2 cones as control on a non-sprayed surface.
        - Frequency: 1 day, 1 week, 2 weeks, 3 weeks, 4 weeks, 2 months, 3 months and 4 months after spraying (or stopped earlier if no mosquito mortality is observed). This will be done after the first application and will be repeated in the second year of application.
  3. Resistance testing of the local Aedes aegypti strains to deltamethrin and other insectcides (as done in baseline) using the WHO standardised impregnated papers (see annex 6 for methodology). Evaluation with one year intervals (starting from baseline): mid 2011, mid 2012 and in 2013 when study finished.

1. Cost-effectiveness evaluation

We will collect during the assay the financial cost of the routine vertical programme and will calculate the average cost per house inspected and treated.

For each arm, we will multiply the number of houses inspected and treated annually during the study by the corresponding average cost described above, to calculate the total annual cost of the routine programme per arm.

We will calculate the total economic cost of the new control tools (ITC and PFS): The economic cost of the community participating in the set up, the financial and economic cost of the routine programme during set up, distribution, installation and maintenance of the tools; and the economic cost of the community participating in collective vector control activities.

The total annual cost of the different arms can be obtained adding the cost of the routine programme and the economic cost of the implemented strategy.

We also will calculate the average and marginal cost per house within arms and incremental cost per house between arms.

The activities of vertical programme will be costed prospectively every month during two years of the study, as well as the cost regarding the distribution of the tools itself, every time it happens (see annex 11-12-13-14-15-16). The cost information about participation in individual and collective activities related to vector control of the community will be followed by questions included in the acceptability survey 3 times during follow up period, in 400 houses per arm for the two intervention arms and with quarterly surveys on the routine activities done (annex 8 ).

We will obtain the effectiveness measure from the entomological and epidemiological study and use the difference of differences between the baseline data and the data for the subsequent periods as effectiveness measure.

We will calculate arithmetic means and 95% confidence intervals when making cost and effectiveness (entomological indices) comparisons between the three arms of the trial. We will carry out incremental analysis, with the mean cost difference between study’s arms divided by corresponding mean difference of entomological indices to give the incremental cost effectiveness ratio (ICER). We will use the non-parametric percentile method for calculating the confidence interval around this ratio with 1000 bootstrap estimates of the mean cost and entomological indices differences. We will carry out sensitivity analysis, varying the price of the tools, and using the variation observed in the correlation between the coverage of tools and the corresponding entomological outcome.

1. Sociological qualitative study on acceptability

In-depth interviews will be conducted in a purposive sample of 20 households where ITC have been distributed and PFS initiated. The households will be identified from data collected by the household survey and through program staff. The interviews will be conducted:

- - 1. 4 months after distribution of ITC and PFS with 10 household heads which have either 1°) not accepted the tools at the onset; 2°) accepted the tools or 3°) accepted with reluctance.
    2. 12 months after distribution of ITC and PFS with 10 household heads which have either 1°) accepted the tools, 2°) accepted with reluctance, and 3°) who have stopped to use them after a period of one year.

The sampling is tentative and could be increased depending on the results of preliminary data analysis. We will also explore the perceptions of the interviewees on the routine *Aedes* *aegypti* control strategy (topics guide and informed consent for in-depth interview: annex 17 and 18).

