## *III.B. Specific objectives*

1. Evaluate the uptake and acceptability of tools in both intervention arms (ITC and PFS)
2. Evaluate the effectiveness of both tools, on top of the routine, in the control of *Aedes aegypti* (in comparison to the effect of the routine programme alone)
3. Compare the cost-effectiveness of both tools with the routine *Aedes* control strategy

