The Breteau index (BI) was on average 2 per 100 houses in 2009. With the interventions, we aim to decrease the BI with 50% to 1/100 houses. Based on the Hayes and Bennett sample size estimation (Hayes & Bennett 1999), using an inter-cluster variation coefficient of 0.5, we need a minimum of 20 clusters of 250 houses in each arm to demonstrate the effect of the ITC or PFS intervention in comparison to the control arm. We increased the number of clusters with 5% and hence will have a final sample size of 21 clusters of 250 houses/study arm. Totaling 63 clusters of on average 250 houses for the entire study.

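### The primary analysis compares several co-primary indices at every survey with no lead outcome or summary over time, and its wording does not match the tool-versus-control contrast that the trial was sized for

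*Protocol*

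**What the plan says.** All references are to the protocol.

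- **Primary outcomes (IV.C, Effect measures):** "Effectiveness: Breteau Index, House index, Pupae per person index, (adult mosquito infestation", followed by "confirmed Dengue cases (if any". None is singled out.
- **Comparison rule (same place):** "Comparison of infestation at each time point between the intervention arms, taking into account the pre-intervention infestation levels and the cluster design".
- **Model (same place):** "Generalized linear random effect regression models with a negative binomial link function will be used".
- **Survey frequency (IV.C, Follow-up surveys):** larval surveys, which include adult collection, follow the routine cycles "with at least one survey per month". For pupae, "The pupal surveys will take place twice a year during the peak periods of infestation (end of April and end of September". The Timeline marks 25 months of entomological evaluation and 5 pupal surveys, counting the month of distribution.
- **Sized question (IV.A):** the calculation uses BI alone and 250 houses per cluster, "to demonstrate the effect of the ITC or PFS intervention in comparison to the control arm".
- **Objective 2 (III.B):** effectiveness of both tools on top of the routine, "in comparison to the effect of the routine programme alone".

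**The concern.** The plan prescribes a comparison at each time point on each primary index. If each comparison is read at 0.05, the trial has many chances to declare a primary effect when there is none. Results for different months and indices may then disagree, with no rule for which one decides. Three analysts could choose different indices, months and contrasts, and each could claim to have followed the protocol.

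Two further costs follow. Month-by-month testing gives up the precision of some 24 repeated surveys of the same clusters. The sentence also speaks of the intervention arms, although other parts of IV.C set intervention areas apart from control areas. Read literally, it leaves out the contrast on which the sample size rests.

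**Working it through.** **1. Reproduce the stated sample size.** Inputs from IV.A: control BI 0.02 per house, target 0.01, between-cluster coefficient of variation k = 0.5, y = 250 houses. Alpha and power are not stated; two-sided 0.05 and 80% are assumed because they reproduce the stated figure.

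Hayes-Bennett: c = 1 + (1.96 + 0.84)² × [(0.02 + 0.01)/250 + 0.25 × (0.0004 + 0.0001)] / 0.01²

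- Bracket: 0.000120 + 0.000125 = 0.000245; divided by 0.0001 this is 2.45.
- c = 1 + 7.85 × 2.45 = 20.23, against the stated 20 (20.07 with the version for proportions).
- 20 × 1.05 = 21 per arm, and 3 × 21 = 63. Both match.

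With y = 250, the calculation describes one contrast on BI at one survey.

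**2. Count the tests.** After the distribution month there are about 24 monthly surveys and 4 pupal surveys. Per contrast: BI, House index and adults × 24, plus pupae × 4, gives 3 × 24 + 4 = 76. Two contrasts against control give 152. Dengue cases are not counted.

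**3. Bound under independence**, 1 − 0.95^m:

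| Tests (m) | At least one p < 0.05 | Expected false positives |
|---|---|---|
| 24 (BI, one contrast) | 70.8% | 1.2 |
| 76 (all, one contrast) | 98.0% | 3.8 |
| 152 (all, two contrasts) | 99.96% | 7.6 |

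These are upper figures. The same clusters are resurveyed, and BI and House index overlap.

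**4. Allow for correlation, BI alone.** Simulation with no true effect: BI 2 per 100, 21 clusters per arm, 250 houses, total between-cluster coefficient of variation 0.5, and a cluster-level t-test at each of 24 months. The share of between-cluster variance that persists over months is an assumption.

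| Persistent share | One contrast | Two contrasts vs control |
|---|---|---|
| 100% | 41% | 63% |
| 50% | 60% | 82% |
| 20% | 68% | 88% |

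A single test of the 24-month mean rejects in about 5-6%. The rate stays high even with full persistence because counts are small. The expected count per cluster and survey is 250 × 0.02 = 5. Poisson variance is 5 and between-cluster variance is 0.25 × 25 = 6.25, so the correlation between months is only 6.25/11.25 = 0.56.

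**5. Allow for correlation, all 76 tests.** With assumed correlation over time of 0.3-0.9 and between outcomes of 0.5-0.9, the chance of at least one false positive is about 26-96% for one contrast and 42-99.8% for two.

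**6. Power with 21 clusters per arm** = Φ(√(20/V) − z), where V is the bracket divided by 0.0001.

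- One survey: V = 2.45, √(20/2.45) = 2.857. At alpha 0.05, Φ(2.857 − 1.960) = 81.5%. At 0.025, Φ(2.857 − 2.241) = 73%.
- Pooled over 24 surveys, k = 0.5 fully persistent: y = 250 × 24 = 6,000, V = (0.000005 + 0.000125)/0.0001 = 1.30, √(20/1.30) = 3.922. At 0.05, 97.5%; at 0.025, 95%.

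**The case against.** **A reader might infer that tool versus control has no primary test.** The documents do not support this. Objective 2 and the sample size both state that contrast, control clusters get the same entomological surveys, and the cost-effectiveness section compares indices across all three arms. The phrase about intervention arms can be read loosely as the study arms, and the general objective can also be read as comparing the two tools. What stands is loose wording that must be reconciled.

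**A reader might infer that false positives are near certain, with four or five outcomes tested monthly.** That is too strong. Pupal surveys are twice yearly, adult infestation is bracketed, and dengue cases are conditional and fall outside a sentence about infestation. Near certainty needs weak correlation over time; the simulated range for one contrast goes down to 26%.

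**The simulated tests are not the planned model.** The protocol names a random-effects negative binomial regression with baseline adjustment, which could be one longitudinal model with an overall test. The t-tests in step 4 do not adjust for baseline. This is fair as to the exact percentages. But the protocol names no overall test, and removing persistent cluster differences by adjustment would, if anything, make the monthly results less correlated and the error rate higher.

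**The analysis plan may deal with multiplicity.** It may, and an absent adjustment is not the point here. The point is what IV.C positively prescribes: a plan that followed it would inherit the problem, and one that chose a single index, window and contrast would depart from it.

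**Effects over time matter clinically.** This stands. The introduction reports rapidly declining curtain use elsewhere, and IV.B says that residual activity of the spray depends on the surface. Months that disagree need not be chance, so time-specific effects should be kept, but as secondary results.

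**Conclusion.** The point holds in this form. IV.C prescribes a comparison at each survey across several co-primary indices, with no lead outcome and no summary over time, in a trial sized on BI alone for each tool against control. Testing each time point at 0.05 gives a false-positive primary result in about 41-68% of null trials on BI alone for one contrast and 63-88% for two, and every correlation pattern tried stayed far above 5%. The percentages rest on assumed correlations, on 24 surveys after rollout and on unadjusted cluster-level tests. The power figures rest on an assumed two-sided 0.05, and the pooled ones also on k = 0.5 being fully persistent. The contrast wording is an inconsistency between IV.C on one side and III.B and IV.A on the other; it does not show that the control comparison is absent.

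**What to change.** Replace the comparison sentence in IV.C with one primary analysis:

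- **Outcome:** BI over all surveys after rollout.
- **Model:** one random-effects negative binomial model with log link and log houses inspected as offset; arm, survey month and baseline BI as fixed effects; cluster as random effect.
- **Primary contrasts:** ITC versus control and PFS versus control, with multiplicity control such as Holm. This brings IV.C into line with objective 2 and the sample size.
- **Secondary:** House index, pupae per person, adult infestation and dengue cases. Report month-specific or arm-by-time effects here too, so that waning of curtains or spray can still be seen.
- **ITC versus PFS:** an estimate with a confidence interval, with no claim of equivalence from a non-significant difference.
- **Power:** restate it for this analysis, with alpha, sidedness and the assumption on k.

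The cost is protocol wording; the same data are collected. The downside is that month-specific tests are no longer confirmatory, and an average effect can dilute one that wanes. If the sponsor kept a single survey as primary, the two contrasts at alpha 0.025 would have 73% power, and 80% would need 1 + (2.241 + 0.842)² × 2.45 = 24.3, so 25 clusters per arm.

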# IV. Methodology

## *IV.A. Description of study* **and study areas**

The study is planned to take place in urban Santiago de Cuba. Santiago is one of the Cuban municipalities where *Aedes aegypti* foci are most frequently reported, despite continuous surveillance and vector control activities. In 1981 it was affected by an epidemic that spread across the country and in 1997, 2001, 2002, 2006 and 2008 by epidemic outbreaks that remained rather limited. Santiago de Cuba is located in the Eastern part of the island, in the province of the same name. The average temperature oscillates between 30 and 32 °C and rainfall is scarce. The municipality is the most densely populated one of the whole country and has 475 580 inhabitants, of which eighty-seven percent live in the urban zone. There are residential settlements under construction and the periurban neighbourhoods lack adequate sanitary conditions. Water is supplied, on average, every 3 days, but since there were in the last decades major damages to the piped water system, the population is used to store drinking water at home in multiple containers. Garbage collection is sometimes deficient, which leads to accumulation of trash.

Design:

Cluster-randomized controlled trial with 2 years follow up of interventions. Intervention and control clusters will be selected out of all urban municipalities (except Fran Pais and Julian Grimau).

Cluster = a house block with its 4 surrounding house blocks; containing approx. a total of 250 houses

Clusters with the highest infestation – levels (entomological information from January to December 2009) will be selected. The selection procedure will assure that there are no common boundaries between clusters, as a certain spill-over effect can be expected (Kroeger et al. 2006). Afterwards, clusters will be randomly allocated to the control, ITC or PFS intervention arm.

Sample size estimation (based on the effectiveness of curtains, measured through entomological indices):

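### The pupal survey's 23 house-blocks per arm are not 20% of 105, and the random draw is not tied to the clusters at whose level the pupal index is built

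*Protocol*

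**What the plan says.** Section IV.A defines the randomised unit: "Cluster = a house block with its 4 surrounding house blocks; containing approx. a total of 250 houses". The sample-size paragraph in the same section ends with "a final sample size of 21 clusters of 250 houses/study arm", and with 63 clusters over three arms.

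Section IV.C lists the pupae-per-person index (PPI) among the primary effectiveness outcomes: "Effectiveness: Breteau Index, House index, Pupae per person index, (adult mosquito infestation". The baseline entomological survey then sets the pupal sample: "This will be done by a special team in 20% of the house-blocks (randomly chosen: 23 houseblocks/arm". Household size is collected "for the construction of Pupal Index per inhabitant (PPI) at the cluster level". Infestation is to be compared between arms with allowance for pre-intervention levels and for the cluster design.

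The text does not say that the blocks are drawn within clusters. It also does not say that clusters are ignored in the draw.

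**The concern.** Two separate things do not fit.

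First, the percentage and the count disagree once the protocol's own cluster definition and cluster number are put in.

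Second, the sampling rule does not guarantee what the outcome needs. A PPI at cluster level requires at least one surveyed block in every cluster. A random choice of 23 blocks from an arm's pool will miss some clusters and take several blocks in others. A cluster that was never surveyed has no PPI, and no later analysis can supply one. The comparison would then rest on fewer independent units than were randomised, although the planned effort is enough to reach all of them.

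**Working it through.** **Inputs.** Five blocks per cluster (one plus four surrounding) and 21 clusters per arm, from section IV.A. A 20% fraction and 23 blocks per arm, from section IV.C.

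**The plan's own figure.** 21 × 5 = 105 blocks per arm, and 0.20 × 105 = 21. The stated 23 is not reproduced: 23/105 = 21.9%. Other cluster numbers give 20 blocks (20 clusters), 22 (22 clusters) and 23 (23 clusters, since 23/0.20 = 115 = 23 × 5). Only 23 clusters per arm would give the stated count, and the protocol has 21.

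**Coverage under a simple random sample of blocks within an arm.**

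- P(a given cluster has no block) = C(100,23)/C(105,23) = (82 × 81 × 80 × 79 × 78)/(105 × 104 × 103 × 102 × 101) = 0.283.
- Expected empty clusters = 21 × 0.2826 = 5.9 per arm.
- In 200,000 simulated draws the mean was 5.9 and the 95% range 3 to 9. No draw covered all 21 clusters.
- With 21 blocks instead of 23: 21 × C(100,21)/C(105,21) = 6.7 empty clusters.
- With at least one block drawn in each cluster: 0 empty.

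**Precision.** Let the variance of one block's value be 1, with a share ρ between clusters, and let the arm mean be the plain mean of the sampled blocks. Write n_j for the number of sampled blocks in cluster j, and n for their total. The variance is ρ × E[Σ n_j²]/n² + (1 − ρ)/n.

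- 23 blocks, unstratified: E[Σ n_j²]/23² = (1 + 22 × 4/104)/23 = 0.0803. Here 4/104 is the chance that a second sampled block falls in the same cluster as the first.
- 21 blocks, one per cluster: 1/21 = 0.0476 at any ρ.
- 23 blocks, one per cluster plus a second in two clusters: Σ n_j²/23² = (19 × 1 + 2 × 4)/529 = 0.0510.

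| ρ | 23 unstratified | 21, one per cluster | 23 within clusters | Unstratified 23 vs 21 |
|---|---|---|---|---|
| 0.20 | 0.0508 | 0.0476 | 0.0450 | +7% |
| 0.50 | 0.0619 | 0.0476 | 0.0473 | +30% |

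Break-even against 21 blocks: 0.0803ρ + (1 − ρ)/23 = 1/21 gives ρ ≈ 0.11. Below that share, the two extra blocks outweigh the uneven spread. Against 23 blocks drawn within clusters there is no such threshold: the (1 − ρ)/23 term is common to both, and 0.0510 is below 0.0803. The within-cluster draw is therefore equal at ρ = 0 and more precise at any share above zero.

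**The case against.** The strongest reply is that the protocol is silent on stratification. A reader might infer that it states a draw without regard to cluster; it does not. Twenty-three blocks are enough for one per cluster with two over, and building the PPI at cluster level would fit such a draw. This stands, so the result must be conditional. The plain reading is still an unstratified draw. When the protocol wants a spread over strata it says so: for the spray bioassays in section IV.C, the randomly chosen houses are taken one in each district. No rule here allots the two extra blocks.

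A reader might also infer that the miscount produces the empty clusters. It does not: the count that matches 20%, drawn the same way, would leave slightly more of them (6.7 against 5.9). Real clusters may also not all have exactly five blocks. If an arm had 115 blocks (ten clusters of six and eleven of five), 23 would be 20%, but the protocol does not say this, and the expected number of empty clusters would still be 6.1.

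On size, the objection is partly right. The sample size rests on the Breteau index, which comes from inspection of all houses and is untouched. Clusters are missed at random, so nothing is biased, and random-effects models can handle unequal cluster representation.

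The between-cluster share for PPI is unknown. A rough guide from the Breteau index assumes Poisson counts, 250/5 = 50 houses per block and the protocol's variation coefficient of 0.5:

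- At 2 per 100: (0.5 × 0.02)² = 0.0001 between clusters against 0.02/50 = 0.0004 within, so ρ = 0.20.
- At 1 per 100: 0.000025 against 0.0002, so ρ = 0.11.

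That points to the low end of the range, but PPI may behave differently.

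**Conclusion.** The point holds in two parts. The count and the percentage conflict (21 against 23 blocks per arm), which is a small slip. The more important part is that the stated draw is not tied to the cluster, for a primary outcome defined at cluster level. On the plain reading, about 6 of 21 clusters per arm (3 to 9) would have no PPI; with a within-cluster draw, none.

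The cost is precision only. The variance is about 7% to 30% higher than with one block per cluster if ρ is 0.20 to 0.50, which is 3% to 14% on the standard error (√1.07 and √1.30). There is no loss against 21 blocks if ρ is below about 0.11. The range for ρ is an assumption, and the calculation takes equal blocks and a plain block mean.

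A reader might go from 21 clusters to 15 and infer a standard error 18% larger (√(21/15)). That treats each remaining cluster as having a single block, when 23 blocks are surveyed and some clusters have several. It lies above the range found here and should not be used.

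**What to change.** In section IV.C, state that the blocks are drawn within clusters, with at least one randomly chosen block in each of the 21 clusters of every arm. Make the count agree with the percentage in one of two ways:

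- 21 blocks per arm, one per cluster, which is exactly 20%; or
- 23 blocks per arm, with two clusters chosen at random for a second block, restated as about 22%.

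The first saves two blocks per arm. The second keeps the planned effort and is at least as precise as the unstratified draw whatever the between-cluster share. Neither adds fieldwork, but the draw must be made this way before the baseline survey.

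The fix does not require the same block to be kept at every round. Positive containers are emptied at each survey, so repeated visits could change the surveyed blocks relative to the rest of their cluster. Fixed or fresh blocks is a separate choice.
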